#### Duration of follow Up

Patients will be followed for 5 years after removal from study or until death, whichever occurs first. Patients removed from study for unacceptable adverse events will be followed until resolution or stabilization of the adverse event.

### Statistical analysis

#### Sample size and accrual

The primary objective of this study is to determine if 5 fractions of MRgRT does not increase GI or GU toxicity over 20 fractions of MRgRT. The primary endpoints are change scores in the bowel (GI) or urinary (GU) domains of the EPIC. The change scores will reflect the 2-year score minus the pre-treatment (baseline) score. It is hypothesized that the EPIC mean change score will be no worse in the 5-fraction arm than it is in the 20-fraction arm for both GI and GU toxicity. The sample size is calculated based on a non-inferiority design. The non-inferiority margins are set to be a change score of 6 points for the GI symptoms and 5 points for the GU symptoms. The standard deviation of the change scores are assumed to be 13.2 for the GI symptoms and 10.5 for the GU symptoms based on estimates in the RTOG 0415 trial [29]. This level of change in scores seems to be clinically meaningful. A sample size of 122 with 61 in each arm will provide 80% power for the GI endpoint and 83% power for the GU endpoint to detect non-inferiority using a one-sided, two-sample t-test with 0.05 level significance. Adjusting for a projected 10% EPIC/non-compliance rate, we will accrue and randomize a total of 136 patients (68 per arm). The primary endpoint analysis will occur approximately 4 years after study activation.

#### Data analysis

##### Analysis of primary endpoints

The co-primary endpoints are GI and GU toxicity as measured by the bowel and urinary EPIC domains, respectively. The change scores, calculated as baseline score subtracted from 2-year score, will be analyzed using a non-inferiority t-test based on the prespecified non-inferiority margins with a significance level of 0.05. If the data are determined to be non-normal, a Wilcoxon test may be used instead. All patients with EPIC bowel and urinary domain scores will be included in the primary endpoint analysis. The EPIC scoring manual will be followed which requires ≥ 80% of items in a domain to be completed in order to obtain a score for that domain.

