### Evaluation of randomization and blinding

This study will employ a randomized phase II non-inferiority design to compare 5 fractions of ultra-fractionated MRgRT versus 20 fractions of moderately hypofractionated MRgRT in the salvage setting for prostate cancer patients after prostatectomy. Patients will be stratified according to baseline EPIC bowel and urinary domain scores (*i.e.,* high bowel score and high urinary score vs. high bowel score and low urinary score vs low bowel score and high urinary score vs. low bowel score and low urinary score) as well as pelvic radiotherapy and androgen therapy (*i.e.,* yes vs. no), for these factors are expected to be associated with the primary outcome. Within each strata, patients will be randomized 1:1 to receive 5 fractions or 20 fractions using permuted block randomization. The trial schema is displayed in Fig. 1.

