##### Analysis of secondary endpoints:

Secondary safety endpoints: Between treatment arms differences in each safety endpoints measured as change in domain specific EPIC scores at a specific time points (*i.e.,* end of RT, 3, 6, 12, 24, and 60 months) from base line will be evaluated using t-test or Wilcoxon rank sum test whichever is more appropriate. The domain specific EPIC scores measured over time will also be modeled using a linear mixed effects model with fixed effects including time points, treatment arm, Gleason score, baseline PSA, T-stage, age, race, and a random intercept. Between treatment arms differences in GI and GU EPIC scores at 2 years adjusting for baseline scores and other covariates will be assessed using analysis of covariance (ANCOVA). Results from the primary unadjusted analysis and covariates adjusted analysis are expected to lead to similar conclusions. Otherwise, further investigation concerning possible heterogeneous subgroup effects and/or the impacts of missing values will be carried out to ensure that meaningful conclusions can be made.Secondary efficacy endpoints: For competing-risk endpoints such as PCSM, local failure (LF), regional failure (RF), TTP, and DM, Gray’s cumulative incidence method will be used with death as a competing risk for LF, RF and DM and death not due to prostate cancer for PCSM and TTP. OS and FFBF will be estimated by the Kaplan–Meier method and compared between arms with the log-rank test. Cox regression will be used to obtain hazard ratios (HRs) for OS and TTP. Fine and Gray’s regression will be used for the endpoints with competing risks. Adjusted HRs and the respective 95% confidence interval will be computed. Baseline PSA, stratification variables (baseline EPIC score and ADT status), age, race, and other covariates (Gleason, T-stage), will be adjusted for as appropriate in this analysis.

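### The primary test is an unadjusted t-test on change scores, although baseline EPIC, nodal radiotherapy and ADT are stratified on and expected to be prognostic; it is valid but may give up precision that a primary ANCOVA would keep

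*Protocol article*

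**What the plan says.** Under Analysis of primary endpoints, the change scores (2-year minus baseline) "will be analyzed using a non-inferiority t-test based on the prespecified non-inferiority margins with a significance level of 0.05", with a Wilcoxon test as a fallback for non-normal data. No covariate or stratification factor is named for this test.

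Under Evaluation of randomization and blinding, allocation is stratified on the four high/low combinations of baseline EPIC bowel and urinary score, on pelvic radiotherapy and on androgen therapy, "for these factors are expected to be associated with the primary outcome".

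Under Analysis of secondary endpoints, arm differences in 2-year GI and GU scores "adjusting for baseline scores and other covariates will be assessed using analysis of covariance (ANCOVA"). The same paragraph calls the t-test the primary unadjusted analysis. It expects the two analyses to agree and provides for further investigation if they do not. For the secondary efficacy models, the adjustment list names "stratification variables (baseline EPIC score and ADT status"); pelvic radiotherapy is not in that list.

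Under Sample size and accrual, power is computed "using a one-sided, two-sample t-test with 0.05 level significance".

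**The concern.** A change score does use the baseline value, but it fixes the baseline slope at 1. ANCOVA estimates the slope from the data. In a randomized trial it targets the same mean difference and, in large samples, is at least as precise. Randomizing within strata that predict the outcome and then leaving those strata out of the test has a second effect. The arms are more alike than the t-test's standard error allows for, so the test rejects less often than its nominal level.

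In a non-inferiority trial an interval wider than necessary raises the chance that a regimen which is truly no worse fails to show it. The information needed to narrow the interval is already collected, and the adjusted model is already planned, but it does not carry the primary conclusion.

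**Working it through.** **Inputs from Sample size and accrual.** One-sided alpha is 0.05 and there are 61 evaluable patients per arm. For the margins: "The non-inferiority margins are set to be a change score of 6 points for the GI symptoms and 5 points for the GU symptoms". The change-score SDs are "assumed to be 13.2 for the GI symptoms and 10.5 for the GU symptoms". The true difference is not given as a number. I take it as 0 from the hypothesis that "the EPIC mean change score will be no worse in the 5-fraction arm than it is in the 20-fraction arm"; this reproduces the stated power.

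**Step 1: the plan's own figure.** SE = SD × √(2/61); noncentrality = margin/SE; power from the noncentral t with 120 df (critical value 1.658).
- GI: SE = 13.2 × √(2/61) = 2.390; 6/2.390 = 2.510; power 80.3% (stated 80%).
- GU: SE = 10.5 × √(2/61) = 1.901; 5/1.901 = 2.630; power 83.4% (stated 83%).

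The sample size is right for the test named.

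**Step 2: variance under ANCOVA.** Let s be the baseline SD, ks the 2-year SD and r their correlation.
- Change-score variance: s²(1 + k² − 2rk).
- ANCOVA residual variance: s²k²(1 − r²).
- Ratio: k²(1 − r²)/(1 + k² − 2rk). For k = 1 this is (1 + r)/2. It equals 1 when rk = 1, because the true slope is then the 1 that the change score assumes.

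Neither r nor k is in the document, so both are assumptions and are varied.

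**Step 3: power with the same 122 patients, margins and alpha.** The change-score SD is multiplied by the square root of the ratio, with 119 df.

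| r | k | Variance ratio | GI power | GU power |
|---|---|---|---|---|
| t-test | – | 1 | 80.3% | 83.4% |
| 0.3 | 1 | 0.650 | 92.7% | 94.5% |
| 0.5 | 1 | 0.750 | 89.2% | 91.5% |
| 0.7 | 1 | 0.850 | 85.6% | 88.3% |
| 0.9 | 1 | 0.950 | 82.0% | 85.0% |
| 0.5 | 1.25 | 0.893 | 84.1% | 86.9% |
| 0.7 | 1.25 | 0.981 | 80.9% | 84.0% |
| 0.7 | 1.5 | 0.998 | 80.3% | 83.5% |

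Example (GI, r = 0.5, k = 1): SD = 13.2 × √0.75 = 11.43; 6/(11.43 × √(2/61)) = 2.899; power 89.2%. Spending two more degrees of freedom on nodal radiotherapy and ADT (117 df) lowers these figures by less than 0.1 point.

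**Step 4: effect of stratified allocation.** This was simulated 20,000 times per r with GI inputs and k = 1. Patients were allocated in permuted blocks of 4 (block size assumed) within high/low baseline strata.

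| r | Rejection at the margin: t-test | ANCOVA | Power: t-test | ANCOVA |
|---|---|---|---|---|
| 0.3 | 3.2% | 5.3% | 83.2% | 92.6% |
| 0.5 | 3.5% | 4.9% | 82.1% | 89.1% |
| 0.7 | 4.5% | 5.3% | 81.5% | 85.5% |

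The t-test is conservative. With stratification counted, its GI power is 1 to 3 points above the 80.3% of Step 1, so the GI gain from ANCOVA is about 9, 7 and 4 points at r = 0.3, 0.5 and 0.7.

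**The case against.** **The t-test is not an error.** The trial was sized for a two-sample t-test and runs one, the power reproduces, and the test errs on the conservative side. This stands: the point is one of efficiency, not validity.

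**The gain may be small.** Scores near a ceiling at baseline (strata cut at 96 and 84) could spread more widely after treatment, giving k above 1. The gain then shrinks, to nil for GI at r = 0.7 and k = 1.5. This also stands. No single value of r or k can be put forward as the expected one. ANCOVA power was not below t-test power in any case computed.

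**Stronger readings that the document does not support.**
- A reader might infer that it is open which analysis decides. It is not: the t-test sits under the primary heading and is called primary again where the ANCOVA is described. Further investigation after disagreement concerns interpretation and does not move the primary test.
- A reader might take the list without pelvic radiotherapy to be the covariate set of the EPIC ANCOVA. It belongs to the secondary efficacy models, and the full ANCOVA covariate list may properly stand in an analysis plan not shown.
- A reader might count a further gain from nodal radiotherapy and ADT. Nothing in the document allows a figure, and the two share the same indications under General concomitant medication and supportive care guidelines, so they may overlap heavily.
- A reader might fold in the joint power for both endpoints. That is a separate sample-size question and is not counted here.

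**Conclusion.** The point holds as a recommendation on efficiency. The primary test makes no use of the stratification factors as covariates and fixes the baseline slope at 1, while the more efficient model is kept as secondary without a stated reason. Against the nominal t-test figure, the gain in GI power runs from nil (r = 0.7, k = 1.5) to about 12 points (r = 0.3, k = 1). For GU it runs from nil to about 11 points. These figures assume a true difference of 0, 61 evaluable per arm, the stated change-score SDs and a linear baseline relation; r and k are assumptions throughout. The validity of the planned test is not in question.

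**What to change.** By a documented amendment, made before any between-arm 2-year EPIC data are seen:
- Make the primary analysis an ANCOVA of the 2-year domain score (or change score) on arm, continuous baseline score of that domain, pelvic nodal radiotherapy and ADT.
- Conclude non-inferiority for a domain if the lower one-sided 95% limit of the adjusted difference (5-fraction minus 20-fraction) lies above −6 for GI and above −5 for GU. The margins carry over because the target difference is the same. This pairing follows Sample size and accrual; the Early stopping guidelines attach the two values the other way round, which must be reconciled separately.
- Keep the unadjusted t-test as a sensitivity analysis.

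Separately, add pelvic nodal radiotherapy to the stratification variables named for the secondary efficacy models, to match the randomization section.

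The cost is a few degrees of freedom and the amendment itself. The amendment is more than a wording change: the declared primary test would change during the trial, and the planned interim look already compares 6-month EPIC change by arm, so the record should show that the decision was made without knowledge of arm differences. No patients, visits or data are added.

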**Fig. 1 Fig1:**
[figure not shown]
Trial Schema. Expanded Prostate Cancer Index Composite (EPIC), EuroQol-5D index (EQ-5D) and International Prostate Symptom Score (IPSS) quality of life (QoL) surveys are collected at baseline, end of salvage radiotherapy, and at 3 month, 6 month, 12 month and 60 month follow up. GI, gastrointestinal; GU, genitourinary; RT, salvage radiotherapy. *EPIC score groups defined as: high bowel score > 96, low bowel score ≤ 96, high urinary score > 84, low urinary score ≤ 84. **Patients with PSA > 0.4 ng/mL, high-risk Decipher genomic classifier scores, or pathologically node positive disease will receive pelvic nodal radiotherapy and androgen deprivation therapy (ADT) as per the clinician’s discretion

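### The co-primary margins are set on mean EPIC change, but the plan lets a Wilcoxon test replace the t-test, and that test respects a mean margin only under a pure location shift

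*Protocol article*

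**What the plan says.** Sample size and accrual puts the whole design on the mean:

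- Hypothesis: "It is hypothesized that the EPIC mean change score will be no worse in the 5-fraction arm than it is in the 20-fraction arm".
- Margins: "The non-inferiority margins are set to be a change score of 6 points for the GI symptoms and 5 points for the GU symptoms".
- Variability: "The standard deviation of the change scores are assumed to be 13.2 for the GI symptoms and 10.5 for the GU symptoms".
- Power: "A sample size of 122 with 61 in each arm will provide 80% power for the GI endpoint and 83% power for the GU endpoint", "using a one-sided, two-sample t-test with 0.05 level significance".

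Analysis of primary endpoints makes a non-inferiority t-test against those margins the primary analysis, and then permits a replacement: "If the data are determined to be non-normal, a Wilcoxon test may be used instead". Early stopping guidelines also works with a mean difference. The Wilcoxon option is therefore the only part of the co-primary decision rule that leaves the mean scale.

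**The concern.** The replacement is chosen after the data are seen, and it changes the question. The t-test asks whether the mean in the 5-fraction arm is less than 6 (or 5) points worse. A Wilcoxon test with the margin added to the 5-fraction arm asks whether a randomly chosen 5-fraction patient, credited with the margin, tends to rank above a randomly chosen 20-fraction patient. The two questions agree when every patient loses the same amount. They part when a few patients lose a great deal, because large drops pull the mean down in full while ranks count them only as low.

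That pattern matters for a toxicity endpoint, and it also tends to make the data look non-normal, which is the condition for the switch. What is at stake is a false declaration that five fractions are non-inferior on bowel or urinary function.

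**Working it through.** **1. The plan's own figures.** Inputs: n = 61 per arm, one-sided alpha 0.05, margins 6 and 5, SDs 13.2 and 10.5. Power ≈ Φ(m / (SD·√(2/61)) − 1.645), with √(2/61) = 0.1811.

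- GI: 6 / (13.2 × 0.1811) = 2.51, giving Φ(0.865) = 80.7% (80.3% with the exact t distribution). Stated: 80%.
- GU: 5 / (10.5 × 0.1811) = 2.63, giving Φ(0.985) = 83.8% (83.4% exact). Stated: 83%.
- 122 / 0.9 = 135.6, so 136. Stated: 136.

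All reproduce. The sample size is not in question.

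**2. What the margin-shifted Wilcoxon tests.** Let the control change be normal with core SD σ. In the 5-fraction arm a share p loses an extra D points, with p·D = m, so the true mean difference is exactly −m and a correct test should pass about 5% of the time. After m is added to the 5-fraction arm, the chance that a 5-fraction value exceeds a control value is

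θ = (1 − p)·Φ(m / (σ√2)) + p·Φ((m − D) / (σ√2)).

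The Wilcoxon has its nominal size when θ = 0.5, which a pure shift gives. Example, GI with p = 0.20, D = 30, σ = 13.2: σ√2 = 18.67, so θ = 0.8 × Φ(0.321) + 0.2 × Φ(−1.286) = 0.8 × 0.626 + 0.2 × 0.099 = 0.521. The standard error of the estimated θ is about √(123 / (12 × 61²)) = 0.0525, so the pass rate is about 1 − Φ(1.645 − 0.021/0.0525) ≈ 10–11%.

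**3. Simulation of the same cases** (61 per arm, one-sided 0.05; p, D and the core SD of 8 are assumptions, not in the documents):

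| Domain | p, D | Core SD | θ | Wilcoxon passes | t-test passes |
|---|---|---|---|---|---|
| GI | 20%, 30 | 13.2 (protocol) | 0.521 | about 10% | about 5% |
| GI | 15%, 40 | 13.2 (protocol) | 0.537 | about 17% | about 6% |
| GU | 17%, 30 | 10.5 (protocol) | 0.534 | about 15–17% | about 6% |
| GI | 20%, 30 | 8 (assumed) | 0.565 | about 35% | about 6% |
| GI | 15%, 40 | 8 (assumed) | 0.597 | about 59% | about 7% |
| GU | 17%, 30 | 8 (assumed) | 0.561 | about 32% | about 6% |

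Repeat runs differ by a point or two.

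**4. Why two core SDs.** The minority's drop itself adds variance. In the first row the pooled SD is √(13.2² + ½ × 0.2 × 0.8 × 30²) = √(174.2 + 72) = 15.7, above the planned 13.2. With core SD 8 it is √(64 + 72) = 11.7, below it. The two settings bracket the planning value in that scenario, so neither is reported alone.

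**5. Cases where the test behaves.** Under a pure shift the Wilcoxon passes about 5%, also with heavy-tailed or skewed data. With graded toxicity (40% lose 5–25 points, mean 0.4 × 15 = 6) it passes about 5.5–6% at SD 13.2 and about 10% at SD 8. With 30% affected and a normal core at the protocol's SDs it passes about 7%.

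**The case against.** The strongest reply is that the inflation depends on the assumed pattern. No distribution of change scores is given, the modelled minority is severe, and the 20-fraction arm is given no severe cases at all. With the protocol's SDs the excess is moderate. Non-normality alone does no harm; unequal shape does. All of this stands and is why a range is reported. The problem does not vanish when both arms contain severe cases, however: at core SD 8, with 10% affected in one arm against 25–30% in the other, the Wilcoxon still passes 18–36%.

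Three stronger readings are tempting, and the article does not support them.

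- *The switch is almost certain to happen.* The cut-points "high bowel score > 96, low bowel score ≤ 96, high urinary score > 84, low urinary score ≤ 84" suggest a ceiling for patients with a high bowel score, if the domain is taken to end at 100. That covers one stratum, and the argument is weaker for urinary scores. In the scenarios with the protocol's SDs, a Shapiro-Wilk check would trigger the switch in roughly a third to three-quarters of trials, and the article names no such check.
- *A non-significant ordinary Wilcoxon would be read as non-inferiority.* The Wilcoxon is offered in place of a test built on the margins, so the natural reading is a margin-shifted version. That is the one used here.
- *The missing criterion for non-normality is itself an error.* An article may leave that detail to a fuller document. The criticism is confined to the sentence that permits replacement.

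The baseline-adjusted ANCOVA under Analysis of secondary endpoints is mean-based, with further investigation promised if it disagrees with the primary result. It is a partial safeguard, but it does not decide non-inferiority.

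**Conclusion.** The point holds in limited form. The stated rule allows a confirmatory test that does not match the hypothesis, margins and power of the trial. Where excess toxicity is concentrated in 15–20% of the 5-fraction arm and the mean difference lies on the margin, false non-inferiority rises from about 5–7% with the t-test to about 10–17% with the Wilcoxon at the protocol's SDs, and to about 32–60% with an assumed core SD of 8. These sizes rest on the assumed share, drop and background, with scores not bounded. They are rates given that the Wilcoxon is used; how often it would be used cannot be derived from the article. The sample size and power statements are correct. The sentence should be changed before the primary analysis.

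**What to change.** Remove the Wilcoxon replacement for the two co-primary endpoints. Base each non-inferiority decision solely on the difference in mean change and its one-sided 95% confidence bound, compared with −6 (GI) and −5 (GU), using a Welch, robust or bootstrap standard error if the data are skewed. Report the Wilcoxon only as a descriptive or sensitivity analysis.

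This costs one sentence. N stays at 136 and power at 80% and 83%. Two things are given up. The mean-based test runs slightly above nominal size under extreme skew, up to about 7% in the scenarios above. And if the arms truly do not differ and the data are heavy-tailed or skewed, the Wilcoxon would have had more power (about 96–98%, against 81–85% for the t-test), but for a hypothesis other than the one the margins define.

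### The primary non-inferiority test is an unadjusted complete-case comparison, so missing 2-year EPIC scores that differ by arm would bias it, and no stated safeguard reliably checks for this

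*Protocol article*

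**What the plan says.** **Primary test and population.** Under Analysis of primary endpoints, the 2-year minus baseline change scores "will be analyzed using a non-inferiority t-test based on the prespecified non-inferiority margins with a significance level of 0.05", with a Wilcoxon test as the alternative if the data are not normal. The population is then fixed: "All patients with EPIC bowel and urinary domain scores will be included in the primary endpoint analysis". The scoring rule "requires ≥ 80% of items in a domain to be completed in order to obtain a score for that domain", so a partly completed form can also count as missing.

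**Allowance for missing scores.** Under Sample size and accrual, the only provision is a larger sample: "Adjusting for a projected 10% EPIC/non-compliance rate", which takes 122 evaluable patients to 136 randomised.

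**Other uses of EPIC.** Under Analysis of secondary endpoints, the article plans:
- comparisons of change scores at each visit;
- a linear mixed model over time with "fixed effects including time points, treatment arm, Gleason score, baseline PSA, T-stage, age, race, and a random intercept";
- a covariate-adjusted ANCOVA at 2 years that includes the baseline score.

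The same section says the effect of missing values will be looked into if the adjusted and unadjusted analyses do not lead to similar conclusions. The early stopping guideline uses 6-month change scores. Table 2 shows EPIC collected at 3, 6, 12 and 18 months after radiotherapy.

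**The concern.** A patient with EPIC at baseline and at every visit to 18 months, but not at 2 years, contributes nothing to the primary test. The extra 10% of patients restores the planned number of evaluable men. It does nothing about which men are missing.

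In a non-inferiority trial this matters in a particular way. If the men lost from the 5-fraction arm are those with the worst bowel or urinary function, and the same is not true to the same extent in the 20-fraction arm, the observed deficit shrinks and a false non-inferiority claim becomes easier. The outcome is patient-reported, and the article describes no blinding for schedules of 2 and 4 weeks, so differential completion is possible. The article gives no evidence that it will occur.

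**Working it through.** **Inputs from Sample size and accrual.** The margins are "set to be a change score of 6 points for the GI symptoms and 5 points for the GU symptoms". The standard deviations of change are "assumed to be 13.2 for the GI symptoms and 10.5 for the GU symptoms". The test is specified as "using a one-sided, two-sample t-test with 0.05 level significance". There are 61 evaluable of 68 randomised patients per arm.

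**Step 1: reproduce the plan's figures.** SE = SD × √(2/61), which is 2.39 for GI and 1.90 for GU. With a true difference of 0, margin/SE is 6/2.39 = 2.51 and 5/1.90 = 2.63. Noncentral t power with 120 degrees of freedom is 80.3% and 83.4%, against the stated 80% and 83%. Also 122/0.90 = 135.6, which rounds up to 136. The plan's figures hold.

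**Step 2: when does complete-case analysis bias the contrast?** Within one arm, the observed mean is too favourable by (missing fraction) × (responder mean − non-responder mean). The bias in the contrast is this shift in the 5-fraction arm minus the shift in the 20-fraction arm. With the same rate and the same gap in both arms, the bias is 0 and type I error stays at 5.0%.

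**Step 3: an assumed adverse scenario.** The gap is not in the document. Assume non-responders in the 5-fraction arm score 5 to 10 points worse than responders, with no gap in the 20-fraction arm, and use the plan's own 10% missing.

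- Bias = 0.10 × 5 to 0.10 × 10 = 0.5 to 1.0 point. That is 8–17% of the GI margin and 10–20% of the GU margin.
- SE = SD × √(2/61.2): 2.386 for GI and 1.898 for GU.
- One-sided type I error, with the true difference at the margin, = 1 − Φ(1.658 − bias/SE).

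| Endpoint | Bias | Bias/SE | Type I error, adverse | Type I error, same size reversed |
|---|---|---|---|---|
| GI | 0.5 | 0.210 | 7.4% | 3.1% |
| GI | 1.0 | 0.419 | 10.8% | 1.9% |
| GU | 0.5 | 0.263 | 8.2% | 2.7% |
| GU | 1.0 | 0.527 | 12.9% | 1.4% |

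The last column replaces the minus sign with a plus: if the gap sits only in the 20-fraction arm, the test becomes conservative. All rates are per endpoint.

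**Step 4: a difference in rates alone is enough.** Assume 15% missing in the 5-fraction arm and 5% in the 20-fraction arm, with the same gap in both. The bias is 0.10 × gap. A gap of 0.5 to 1 SD gives 0.66 to 1.32 points for GI and a type I error of 8.5% to 13.7% (noncentral t).

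**Step 5: does earlier EPIC information help?** A simulation for GI (8,000 replicates per setting) let dropout depend on an earlier score, with about 15–20% missing against 5% and a correlation of 0.5 to 0.7 between the earlier and 2-year scores. Complete-case type I error was 8–13%. An estimator using the earlier score gave 4.9–5.1%. This result holds because dropout was made to depend on an observed score.

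**Step 6: do the stated safeguards catch it?**
- The 2-year ANCOVA needs the same 2-year scores, so it omits the same men.
- Missing values are examined only if the adjusted and unadjusted conclusions differ. Both analyses can be biased alike and agree.
- The mixed model can use men without a 2-year score, but the effects named do not include an arm-by-time term or baseline EPIC. With only those effects it estimates one arm difference common to all visits, not the 24-month contrast.

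**The case against.** Several points on the other side are sound.

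- **The interim EPIC scores are not wasted.** They are compared by visit, modelled over time and used for the futility rule. A reader might infer that the plan ignores them. It does not; they are absent only from the primary test.
- **Outcome-related dropout does not by itself bias the contrast.** It must differ by arm in rate or in selectivity. A reader might also infer that the bias must favour non-inferiority. Nothing in the article fixes the direction, and Table 1 lists lower calculated rectal and bladder BED for 5 fractions (75 against 85 Gy, and 103 against 105 Gy).
- **The mixed-model list is introduced by a word that need not be exhaustive.** An interaction may be specified in the analysis plan, which is not shown. It would go too far to say that the model cannot serve; it can be said only that, as listed, it does not supply the contrast.
- **Tipping-point or delta-adjusted checks are normal analysis-plan content.** Their absence from an article is no fault.
- **The trial is never called open-label.** That is an inference from the schedules and from the lack of any described blinding.

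What these points leave untouched is that the article does fix the primary test and its population, and the checks it names either drop the same patients or depend on a disagreement that may not appear.

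**Conclusion.** The point holds in a conditional form. The primary verdict rests on an unadjusted complete-case comparison that is open to bias in either direction if missing 2-year scores differ by arm. At the plan's own 10% missing rate, the effect runs from none (alike missingness) to a one-sided type I error of about 7–11% for GI and 8–13% for GU in the assumed adverse case. The mirror-image case brings it down to about 2–3% and 1–3%. These figures depend on an assumed 5 to 10 point gap confined to one arm, which the article neither supports nor excludes. They show sensitivity and are not a forecast. The sample size and stated power are not in question. The change is worth making because a better method is available from data the trial already collects.

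**What to change.** Make the primary analysis a repeated-measures model of post-baseline EPIC scores, separately for each domain, in all randomised patients with a baseline EPIC and by assigned arm. Include baseline score, stratification factors, visit, arm and arm-by-visit. Test the 24-month arm contrast against the 6-point GI and 5-point GU margins at the stated one-sided level, and keep the complete-case t-test as supportive. If the sponsor prefers to retain the t-test as primary because the sample size was built on it, the model should at minimum be a sensitivity analysis that is always reported, not one triggered by a disagreement.

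The cost is a change of wording and modest programming, with no new data and no change in sample size. The downside is reliance on missing at random: the model removes only the part of the bias that earlier scores predict, and a decline after the last observed visit would remain.
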